## **6.2 Vital signs & physical examination**

### **Vital signs**

Vital signs will be performed at every visit by a nurse or nurse assistant. Vital signs include heart rate, respiratory rate, blood pressure, body temperature, height, and weight.

### **Physical Examination**

A detailed complete physical exam will include examination of lymph nodes, cardiac and respiratory systems, abdomen, skin, back/spine, and neurology. In addition, various assessment scores will also be performed. Examination and assessment will be recorded in a structured manner. A complete physical exam will only be performed at the screening visit (SCR).

A focused physical exam will be directed only at new symptoms and complaints of the participant to find evidence of active disease. This targeted physical exam may include examination of lymph nodes, respiratory system, abdomen and back/spine and neurology. A focused physical exam will be performed at every visit except the screening visit (SCR).

## **6.3 Medical History & co-medication**

### **Medical History**

A complete medical history will be taken and recorded in a structured format only at the screening visit (SCR). The complete medical history will cover current symptoms, past medical history, occupational history, family and social history, drug history, allergies, and review of systems.

A focused medical history will be taken for cause and recorded in a structured format. The focused medical history will cover new symptoms and review of systems, as needed. A focused medical history will be taken at every visit the screening visit (SCR).

### **Co-medication**

Co-medication will be recorded at screening visits in detail (type, dose, route, frequency) and source documents from the primary care clinics will be used for verification. This information will be updated at every follow-up visit throughout the study. All co-medication will be recorded on the co-medication.

## **6.4 Sputum and urine collection**

### **Sputum induction**

Sputum induction at screening will take place in a designated area. Hypertonic saline will be administered via the mouthpiece of a nebulizer to induce expectoration. Staff members assisting participants will wear N95 respiratory protection masks. Sputum induction is not required if the participant can produce sputum without induction.

### **TB culture (MGIT)**

Sputum and urine will be cultured on liquid media (Mycobacteria Growth Indicator Tube, MGIT) at screening visit to determine pulmonary TB status. Contaminated cultures will be considered “no test”, i.e., neither culture positive nor negative, and will be repeated. To note, if a culture is contaminated or otherwise not evaluable, another sputum sample may be requested prior to the next study visit. Isolates of positive MGIT cultures will be harvested and stored. This includes also positive Mtb cultures of another site of disease.

### **GeneXpert Ultra**

GeneXpert Ultra will be performed at screening visits to determine pulmonary TB status. GeneXpert Ultra will be used to measure cycle threshold (the amplification cycle when Mtb DNA becomes detectable in the Xpert assay) as a surrogate marker for bacterial load. Gene Xpert Ultra may be done if sputum or sputum sediment is available.

## **6.5 Blood collection**

Approximately 50 mL of blood will be drawn at each time point as indicated on the study timelines. Samples will be processed in the haematology and biochemistry laboratories of the National Health Laboratory Service according to local SOP and the research laboratories. Testing may be repeated to check for or follow-up on abnormal results when needed, for example, at screening or after learning about an adverse event.

### **Full blood count**

Up to 4 mL of blood will be collected in an EDTA tube for haematology (full blood count and differential).

### **Serum chemistry**

Up to 5 mL of blood will be collected in a clot activator tube (with or without gel) for serum collection. The serum can be used for performance of ALT, creatinine and hsCRP.

### **HBA1C**

Up to 4 mL of blood will be collected in an EDTA tube for HBA1C.

### **HIV-1 testing**

Up to 5 mL of blood will be collected in a clot activator tube (with or without gel) for serum collection. The serum will be used for HIV-1 ELISA test for all participants not on ART.

### **CD4 count**

Up to 4 mL of blood will be collected in an EDTA tube for HB

### **HIV-1 viral load**

Up to 3 mL of blood will be collected in an EDTA tube for

### **Blood biobanking - immunological markers**

Up to 4 mL will be collected in an SST tube (serum separator tube) for immunological markers (cytokines, chemokines, soluble mediators).

### **Blood biobanking – PBMC isolation**

Up to 36 mL will be collected for sodium heparin tube for PBMC isolation for macrophage assays, confocal and CFU assays.

### **Blood biobanking – blood for host mRNA**

Approximately 5 mL blood will be collected in two separate PAXgene tubes (2x2.5 mL) for determining host mRNA signatures at three different time points: baseline, 6 months, 12 months.

Analysis will be performed by a third-party company (Inflammatix), any other academic group or the South African MRC.

#### **6.6 SARS-CoV-2 testing**

Naso- or oro-pharyngeal swap for SARS-CoV-2 RT-PCR or Rapid Ag testing will be performed if symptomatic or required for the MRI, PET/CT or any other protocol investigation. Serum sample may be used for SARS-CoV-2 antibody testing.

#### **6.7 Finger prick**

A fingerprick will be performed for a test for blood glucose levels.

#### **6.8 Urine beta-hCG**

Urine will be collected for pregnancy testing before each PET/CT scan. A commercial human chorionic gonadotropin (beta-hCG) determination assay will be performed in accordance with manufacturers' guidance.

#### **6.9 PET/CT scanning**

The whole-body PET/CT scans will be performed at Cape Universities Body Imaging Centre (CUBIC) at the University of Cape Town (UCT). The CT portion of the scan will be done without contrast. Participants will consent to receive a maximum of 3 PET/CT scans during the study (PET 1, PET 2 and PET 3).

Participants will be fully briefed regarding what to expect and any precautions highlighted. Participants will be asked not to eat for about 6 hours prior to the scan but to drink plenty of water. Participants will have an assessment of blood sugar. A venous cannula will be inserted and approximately 7 mCi of radiolabelled Fluorodeoxyglucose (F) administered. In case of expected incontinence and if the participant is not already catheterized, a urinary catheter will be inserted. After about 50 minutes participants will void urine, and at about 60 minutes after injection, the participants will undergo a whole-body PET/CT. For details of the scanners used, please refer to the appendices.

#### **6.10 Adherence monitoring**

Adherence to ART and/or TB-treatment will be monitored by study staff at visits and via telephonic follow-up.

#### **6.11 Withdrawal or termination from the study**

Participants with significant incidental findings on PET/CT that require immediate diagnostic procedures or treatment may be withdrawn from the study if in the opinion of the investigator, continuing the study may not be in the participant's best interests. Participants will be replaced.

During any stage of the study, participants may be withdrawn and replaced if:

- a) Participant withdraws consent
- b) There is any reason deemed appropriate by the investigator or attending physician.

## **6.12 Study completion**

Participation will be considered completed if the participant completes the final (third) PET/CT.

## **6.13 Analysis**

Analysis will be performed using SPSS®. Continuous data will be analysed as median and interquartile range [IQR] and categorical data as frequencies (%) with their 95% confidence interval (CI) where appropriate. For comparing proportions between two groups, we use the chi-square (v2) test. Medians will be compared between two groups (HIV infected and HIV uninfected) using the Wilcoxon ranksum test. Univariate logistic regression will be performed and the cut-off P-value < 0.2 used for inclusion of variables in the multivariate logistic regression model. Multivariate logistic regression will use a stepwise backwards and manual intelligent techniques to identify the independent predictors of the composite endpoint of MS. The logistic regression models' results will be presented as odds ratios (OR) with the 95% CI. Statistical significance will be accepted at the two-sided level of  $P \leq 0.05$ . Sociodemographic and clinical data as well as laboratory findings will be analysed.

Semiquantitative PET/CT analysis will be performed using MIM® Software. Total lesion glycolysis (TLG) at the region of interest (ROI) will be measured as well as SUVmean, SUVmax and SUVvolume after subthreshold calculation of the ROI.

## **7 Covid-19 Infection**

The coronavirus disease 2019 (COVID-19) is a respiratory viral infection caused by the Severe Acute Respiratory Syndrome Coronavirus 2 (SARS-CoV-2) virus. The SARS-CoV-2 originated in Wuhan, China in December 2019 and was declared a global pandemic by the WHO on March 11, 2020. COVID-19 symptoms include fever, chills, cough, shortness of breath, fatigue, loss of smell and taste, myalgias, and headache amongst others. These symptoms may overlap with those of pulmonary tuberculosis. How a coinfection with SARS-CoV-2 affects the clinical presentation or treatment outcome of pulmonary TB patients is not currently well known.

Covid-19-PCR-tests or Antigen-tests will be performed at any visit according to the present local epidemiology and guidelines.

## **8 Adverse event, serious unanticipated problems, protocol deviations, and non-compliance**

### **8.1 Definitions**

#### **Adverse Event (AE)**

Any untoward medical occurrence in a participant, including any abnormal sign, symptom, or disease, temporally associated with the participant's participation in research, whether or not considered related to the participant's participation in the research.

#### **Serious adverse event (SAE)**

Any adverse event that:

- a) results in death.
- b) is life-threatening (places the participant at immediate risk of death from the event as it occurred).

- c) results in in-patient hospitalization or prolongation of existing hospitalization.
- d) results in a persistent or significant disability/incapacity.
- e) results in a congenital anomaly/birth defect; or
- f) based upon appropriate medical judgment, may jeopardize the participant's health, and may require medical or surgical intervention to prevent one of the other outcomes listed in this definition

### **Protocol Deviation (PD)**

Any change, divergence, or departure from the Institutional Review Board (IRB) approved study procedures in a research protocol. Protocol deviations are designated as serious or non-serious and are further characterized as the following:

- a) Those that occur because a member of the research team deviates from the protocol
- b) Those that are identified before they occur, but cannot be prevented
- c) Those that are discovered after they occur

### **Serious Protocol Deviation (SPD)**

A deviation that meets the definition of a Serious Adverse Event (SAE) or compromises the safety, welfare or rights of participants or others.

### **Unanticipated Problem (UP)**

Any incident, experience, or outcome that meets all three of the following criteria would be considered a serious UP:

1. unexpected in terms of nature, severity, or frequency in relation to
  - the research risks that are described in the IRB-approved research protocol and informed consent document or other study documents; and
  - the characteristics of the participant population being studied
2. related, possibly or probably related to participation in the research
3. suggests that the research places participants or others at a greater risk of harm (including physical, psychological, economic, or social harm) than was previously known or recognized.

### **Unanticipated problem that is not an AE (UPnonAE)**

An unanticipated problem that does not fit the definition of an AE, but which may, in the opinion of the investigator, involve risk to the participant, affect others in the research study, or significantly impact the integrity of research data. These events may involve a greater risk of social or economic harm to participants or others rather than physical/psychological harm. Such events would be considered a non-serious UP. Examples of an UPnonAE include a breach of confidentiality, accidental destruction of study records, or unaccounted-for study drug.

## **8.2 Investigator Assessment of Adverse Events**

### **Grading Adverse Events for Severity**

The severity of each AE will be determined using the corrected version of the Division of AIDS (DAIDS) Table for Grading the Severity of Adult and Pediatric Adverse Events. This table can be found using the following link: DAIDS TOX TABLE (Corrected Version 2.1 July 2017). Any events that are not listed in this toxicity table will be graded by the local investigator as follows:

**Table 1: Adverse event grading**

|                            |                                                                                                                                                              |
|----------------------------|--------------------------------------------------------------------------------------------------------------------------------------------------------------|
| Grade 1 - Mild             | Transient or mild discomfort; no limitation in activity; no medical intervention/therapy required                                                            |
| Grade 2 - Moderate         | Moderate limitation in activity – some assistance may be needed; no or minimal medical intervention/ therapy required                                        |
| Grade 3 - Severe           | Marked limitation in activity; some assistance usually required; medical intervention/therapy required; hospitalizations possible                            |
| Grade 4 - Life-threatening | Extreme limitation in activity, significant assistance required; significant medical intervention/therapy required, hospitalization or hospice care probable |
| Grade 5 - Death            |                                                                                                                                                              |

### **Assessing Adverse Events (AE) for relationship to study**

Any AE that occurs in a participant will be assessed for its relationship to the study. A causal relationship means an intervention caused (or is reasonably likely to have caused) the AE. This usually implies a relationship in time between one or more intervention and the AE - for example, the AE occurred shortly after the participant received the drugs/study agents/intervention.

For all AEs, the clinician who examines and evaluates the participant will determine the AE's causality based upon the temporal relationship to administration of the intervention, the pharmacology of any applicable study agents, and his/her clinical judgment.

The following scale will be used to reflect the PI's judgment as to the relationship between the intervention and the AE:

#### **Definitely Related**

The AE is clearly related to one or more of the interventions – follows a reasonable temporal sequence from administration of one or more of the interventions, follows a known or expected response pattern to the one or more of the interventions that is confirmed by improvement on stopping and reappearance of the event in repeated exposure and that could not be reasonably explained by the known characteristics of the participant's clinical state.

#### **Probably Related**

The AE and administration of the interventions are reasonably related in time and/or follows a known pattern of response, and the AE is more likely explained by one or more of the interventions than other causes.

#### **Possibly Related**

AE follows a reasonable temporal sequence from administration of the interventions, follows a known or expected response pattern to the suspected intervention or interventions, but that could readily have been produced by several other factors.

#### **Unlikely Related**

A potential relationship between one or more of the interventions and the AE could exist (i.e., the possibility cannot be excluded), but the AE is most likely explained by causes other than one or more of the interventions (e.g., could readily have been produced by the participant's clinical state or could have been due to environmental or other interventions)

#### **Unrelated**

AE is clearly not related to one or more of the interventions - another cause of the event is most plausible and/or a clinically plausible, temporal sequence is consistent with the onset of the event and the intervention administration and/or event is biologically implausible.

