**Table 2: Expected adverse events**

| Intervention/potential cause of AE | Adverse effects                                                                    |
|------------------------------------|------------------------------------------------------------------------------------|
| Blood drawing                      | Common: Discomfort                                                                 |
|                                    | Significant but rare: Hematoma, Infection, nerve damage, syncope                   |
| FDG-PET/CT                         | Significant but rare: Hematoma, thrombophlebitis, infection, nerve damage, syncope |
| Induced Sputum                     | Can have coughing, wheezing, and or bronchospasms                                  |

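### In Protocol section 8.2, the Unrelated category treats timing that fits the intervention as a ground for ruling causation out

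*Protocol*

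**What the plan says.** Protocol section 8.2 introduces its causality scale by saying what a causal relationship normally involves: "This usually implies a relationship in time between one or more intervention and the AE". Five grades follow.

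- *Definitely Related* includes a reasonable time sequence among its requirements.
- *Probably Related* begins: "The AE and administration of the interventions are reasonably related in time and/or follows a known pattern of response". The intervention must also be the likelier explanation.
- *Possibly Related* begins: "AE follows a reasonable temporal sequence from administration of the interventions". A recognised response pattern is also needed, while other factors could readily explain the event.
- *Unlikely Related* has no timing criterion. It rests on other causes being the most likely explanation.
- *Unrelated* begins: "AE is clearly not related to one or more of the interventions - another cause of the event is most plausible". It then adds, joined by *and/or*, that "a clinically plausible, temporal sequence is consistent with the onset of the event and the intervention administration", and, again joined by *and/or*, that the event is biologically implausible.

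The grade is used elsewhere. Section 8.3 has the investigator's judgement of relationship entered on the case report form for each reportable event. Section 8.1 defines an Unanticipated Problem by three criteria that must all be met, the second being that the event is "related, possibly or probably related to participation in the research".

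**The concern.** Timing that fits an exposure is the first thing an assessor looks for when suspecting that the exposure caused an event. Here it is offered as a reason to conclude that it did not. Because the grounds are alternatives, an assessor can cite fitting timing alone in support of *Unrelated*. The same feature of the same event supports *Possibly* or *Probably Related* a few lines earlier. Two careful assessors could therefore grade one event at opposite ends of the scale, and each could point to the text.

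At stake are the accuracy of the relationship field in the safety data and the chance that an unexpected event with a plausible link to a study procedure is stopped at the second criterion for an Unanticipated Problem. This is an operative rule that clinicians apply event by event, so it would not ordinarily be left to a statistical analysis plan.

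**Working it through.** The protocol gives no figure to reproduce on this point. The check sets the definitions side by side and then traces where the grade is used.

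**1. Direction of the timing criterion**

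| Place in section 8.2 | Fitting timing counts |
|---|---|
| Introduction to the scale | towards causation |
| Definitely Related | towards causation |
| Probably Related | towards causation |
| Possibly Related | towards causation |
| Unlikely Related | not used |
| Unrelated | against causation |

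Only the last row points the other way.

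**2. Logic of the *Unrelated* definition**

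Call its grounds A (another cause is most plausible), B (timing is consistent with the intervention) and C (biologically implausible). Joined by *and/or*, they read as A or B or C, so B alone is enough.

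Take an event that follows a procedure in reasonable sequence, matches a recognised response to it, and could readily have another cause. It meets *Possibly Related* in full. It also meets B.

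Now replace B by its negation, that timing is *not* consistent with the intervention. The event no longer meets that ground. An event whose timing does not fit the procedure does meet it, as one would expect. Reversing the clause removes the conflict, which suggests that a negation was lost in drafting.

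**3. Where a wrong grade has an effect**

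- Case report form (section 8.3): affected. The relationship judgement is a recorded item for reportable events.
- Unanticipated Problem (section 8.1): affected for some events. One that is unexpected and suggests greater risk meets criteria 1 and 3. Graded *Possibly Related* it also meets criterion 2 and qualifies; graded *Unrelated* it fails criterion 2 and does not.
- Source documents (section 8.3): not affected. All events are recorded, whether related or not.
- Oversight committee (section 10): not affected. Its progress report covers every serious adverse event, with no causality filter.
- Ethics committee and regulator (sections 8.6 and 8.7): cannot be determined. Both follow external procedures that are not reproduced.

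**4. Procedures to which the rule applies**

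Section 4.2 plans 100 participants with three scans each: 100 × 3 = 300 PET/CT cannulations. The schedule in section 5 has blood drawn at screening and at each of the three PET/CT visits: 100 × 4 = 400 blood-draw visits. Bladder catheterisation at scans and sputum induction at screening, where needed, come on top. These are planned counts of procedures at full enrolment and follow-up. They do not measure how many events would be misgraded.

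**The case against.** The strongest reply is that *Unrelated* opens with a governing condition, that the event is clearly not related, and that section 8.2 leaves the grade to clinical judgement. A sensible clinician would have to override both to grade an event *Unrelated* because its timing fits. This makes misuse less likely. It does not cure the text: the grounds are what the definition offers in support of that condition, and one of them supports the opposite.

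A reader might go further and infer that procedure harms are coded out of reporting altogether. The protocol does not support that. Source-document recording and committee review of serious events do not depend on the grade, and section 8.3 does not define a reportable event by causality. The obvious examples also fail for another reason. Table 2 lists for FDG-PET/CT "Significant but rare: Hematoma, thrombophlebitis, infection, nerve damage, syncope", and section 11.1 names infection from the intravenous line and urinary tract infection from a catheter. Such events are expected, so unless unusual in severity or frequency they fail the first criterion for an Unanticipated Problem whatever their grade.

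A reader might also infer that the top of the scale is unreachable, because *Definitely Related* must be "confirmed by improvement on stopping and reappearance of the event in repeated exposure". That does not hold either. Blood draws, cannulation and, where needed, catheterisation recur during the study, so the grade is hard to meet but not impossible; only sputum induction has no scheduled repeat. An event that misses it can still be *Probably* or *Possibly Related*, and either satisfies criterion 2. The protocol attaches no consequence to *Definitely Related* alone.

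**Conclusion.** The point holds, within narrow limits. The timing ground under *Unrelated* is inverted and contradicts the introduction to the scale and its three related grades. Its supportable consequences are a wrong relationship code on the case report form and the loss, at criterion 2, of an unexpected event that would otherwise be an Unanticipated Problem.

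The conclusion rests on two assumptions: that some assessors will follow the wording as written, and that criterion 2 is judged from the section 8.2 grade, which the shared terms imply but the protocol does not state. The number of events affected is unknown. No broader claim, about lost reporting to the ethics committee or regulator or about an unusable top grade, can be drawn from this document.

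**What to change.** In the *Unrelated* definition of section 8.2, reverse the timing ground so that it says the temporal sequence is *not* consistent with the onset of the event and administration of the intervention. Carry the same wording into the causality field of the case report form. *Definitely Related* needs no change on this account.

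The cost is one clause in the protocol and the matching form text, with no added procedure, visit or data item. The downside is that slightly more events may be coded as related.
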